## **7. Assessment of efficacy**

The primary and secondary endpoints of the study are described in section 3 (study design).

## **8. Assessment of safety**

### **8.1 Notification of adverse events and serious adverse events**

Critical illness is a condition with adverse outcomes that are expected to occur. In this study adverse clinical outcomes are listed primary, secondary or safety endpoints. Hence, none of these study outcome endpoints will be considered as serious adverse events or suspected unexpected serious adverse reactions and thus do not need to be reported to the competent authorities. Any other and unexpected adverse reaction will be reported to the study sponsor.

For safety reasons, an interim analysis of hospital mortality will be performed after inclusion of 50% of the study population, with stopping boundaries predefined by the DMC to allow early study termination if the intervention group would appear clearly inferior.

The main adverse event of the intervention is hypoglycemia, which warrants prompt treatment. However, ICU physicians and nurses are familiar with the effects of insulin administration and follow-up of blood glucose concentrations. Hence, reporting hypoglycemic episodes to the competent authorities is not necessary. However, severe hypoglycemia (<40 mg/dl) that is resistant to intravenous glucose administration will be considered as a serious adverse event. This adverse event will be reported to the sponsor, after first knowledge. The immediate report will be followed by detailed, written reports. The sponsor will keep detailed records of all adverse events which are reported to him. These records will be submitted to the competent authorities when requested. In the intervention group, tight glucose control is timely stopped before ICU discharge, so that hypoglycemia provoked by the intervention is not expected to occur after ICU discharge. Therefore, hypoglycemia or other new medical events that would occur after ICU discharge and that would not be listed in the outcome measures will not be considered as adverse events, since these events cannot be attributed to short-acting insulin.

## **8.2 Treatment stopping rules**

As mentioned above, the study intervention (tight blood glucose control) will be discontinued:

- when the patient resumes oral carbohydrate intake (meals, energy-rich drinks)
- when the central venous catheter is removed and not replaced
- upon ICU discharge

As long as the patient fulfills one of these stopping criteria, a liberal blood glucose control strategy will be maintained. When these stopping rules would cease in a patient, the study intervention will be restarted. This may occur when the patient would get sicker again while still in ICU (with placement of new arterial and venous line and interruption of oral feeding), or when the patient would be readmitted to the ICU within 48 hours after ICU discharge.

## **8.3 Data monitoring committee (DMC)**

As mentioned below, a first interim analysis will take place after inclusion of 25% of the study population, to ensure adequate statistical power and adjust sample size if needed.

For safety reasons, an interim analysis of the safety endpoint (hospital mortality) will be performed after the first 4615 patients (50% of the study population), with stopping boundaries

predefined by the DMC to allow early study termination if the intervention would appear clearly inferior.

The independent DMC will also assess protocol compliance. To that purpose, the inclusion/exclusion rate and reasons for exclusion, the time profiles of blood glucose during the first 2 weeks in ICU, the incidence of hypoglycemia in ICU and the amount of enteral/parenteral feeding during the first week in ICU will be reviewed.

## 9. Statistics

### 9.1 Sample size

The sample size is calculated in order to detect, with at least 80% power (two-tailed) and 95% certainty, a reduction in ICU dependency by one day. With a baseline mean ICU stay of 9 days in ICU and a standard deviation of 15, 2782 patients in each group are needed to detect a reduction by one day (total 5564). For safety reasons, we also want to exclude any clinically relevant harmful impact on hospital mortality (safety endpoint). To detect an adversely increased hospital mortality from 8.5% to 10% with 80% power and 95% certainty, 4612 patients per group need to be included (total 9224). Hence, we plan to include 9230 patients.

The baseline mean ICU stay and its standard deviation are based on our previous multicenter RCT (17). As the baseline ICU stay may have changed over time, may differ per center and as it is difficult to predict the relative contribution of each center, we plan an interim analysis after inclusion of 25% of the study population (n=2308). At that time point, the independent data monitoring committee will receive an export of the necessary data (ICU length of stay and ICU mortality) in the control group (liberal blood glucose control) and will calculate a new sample size.

The primary endpoint (ICU dependency) will be analyzed in an unadjusted manner. The crude number of days with need for vital organ support will be compared by Student's t test or non-parametric testing, as appropriate. The time to live discharge from ICU will be documented by Kaplan-Meier plots with use of log-rank/Wilcoxon testing; the time-to-event effect size will be estimated with the use of Cox proportional hazard analysis provided the proportional hazard assumption is valid for the dataset. The ICU mortality will be compared by chi-square test.

We anticipate that 2 years will be needed to take this study to completion (from first inclusion until last inclusion), provided informed consent will be at least 80%.

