### 3. Trial objectives and design

#### 3.1 Trial objectives

The main objective of this study is to test the hypothesis that in adult critically ill patients receiving an evidence-based, restrictive feeding regimen (no parenteral nutrition in the first week of critical illness), targeting normal blood glucose concentrations (80-110 mg/dl) reduces short-term morbidity and dependency on intensive care as compared with tolerating hyperglycemia up to 215 mg/dl. The null hypothesis is that there will be no difference in the primary outcome measures (incidence of new infections during ICU stay, ICU length of stay and the time to live discharge from ICU) between the two strategies. The study is two-tailed so that it is also powered to detect a negative impact of targeting normal blood glucose concentrations. As a safety endpoint, mortality will be monitored. These analyses will be done unadjusted as well as adjusted for risk factors.

The secondary objectives are:

- To study the long-term impact of the intervention (morbidity and mortality)
- To study the economic impact (healthcare resources)
- To study the underlying mechanisms that may explain an eventual benefit (or harm) from targeting normal blood glucose concentrations with intensive insulin therapy (depending on additional funding). This will be achieved by studying the effects of treatment allocation on metabolic, endocrine, inflammatory, coagulation, cardiac and (epi)genetic markers in blood and tissue samples of critically ill patients and by studying the effects of treatment allocation on the innate immune response and pathways of inflammation and autophagy.

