## 6.4 Other investigations

In selected centers, the presence of ICU-acquired weakness will be assessed clinically (see 1. Clinical assessment). In these centers, depending on funding, the clinical assessment will be supplemented by electrophysiological tests, ultrasound, functional tests and muscle biopsy at day 7±1, day 14±1 and day 21±1 in patients still in ICU at that time (see 2. till 5. Below). Additional informed consent will be asked for performing additional electrophysiological tests and muscle biopsies. The patient or his/her legal representative will have the possibility to only consent to a subset of these additional tests. Based on the results from previous studies and a lower anticipated effect size of blood glucose control in patients not receiving early parenteral nutrition, we expect a 12% difference in the electrophysiological incidence of critical illness polyneuropathy/myopathy (26, 27). With an  $\alpha$ - and  $\beta$ -error of 5, respectively 20%, minimum 424 patients need to be included. The electrophysiological findings will be correlated with markers of muscle mass and tissue changes.

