## 9.3 Analysis

A Consolidated Standards of Reporting Trials (CONSORT) diagram will be reported.

For the primary and most secondary endpoints taking place during ICU stay, all data will be available. Of the secondary endpoints, some laboratory measurements may be missing. Missing data for one time point may be interpolated, by calculating the mean of the two neighbor measurements. In other cases, missing data will not be imputed.

All analyses will be done on intention to treat basis. In case of request for discontinuation of the study intervention by the patient or legal representative, this will be respected, but all data that are already collected will be analyzed.

The data file will be finalized and locked 90 days after inclusion of the last patient (except for the post ICU follow-up outcome parameters, as specified above). Discrete variables will be summarized by frequencies and percentages. Continuous variables will be summarized by use of either mean and standard deviation (SD) or median and interquartile range as appropriate. Results will be analyzed with the use of Chi-square testing, Student's t test or non-parametric testing (Wilcoxon rank-sum test, Van der Waerden test or Median test), as appropriate. Time-to-event effects will be documented by Kaplan-Meier plots with use of log-rank/Wilcoxon testing; the time-to-event effect size will be estimated with the use of Cox proportional hazard analysis provided the proportional hazard assumption is valid for the dataset. All time-to-event analyses will also be performed on data censored at 90 days. As death is a competing risk for duration of care outcomes, non-survivors will be censored beyond the longest duration of such care required for survivors.

All outcomes will be analyzed in an uncorrected manner as well as adjusted for baseline risk factors (including type and severity of illness, age, gender, body mass index, history of diabetes or not, center). For these analyses, P-values will be considered significant when at or below 0.05 without correction for multiple testing. To assess whether any eventual impact of the intervention on the primary and safety endpoints is affected by the baseline risk factor subgroup, interaction P-values will be calculated (logistic regression or Cox proportional hazard analysis as appropriate) with a threshold for significance of interaction set at a P-value of <0.1. These a

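### Section 9.1 is labelled two-tailed, but both sample sizes are one-sided 5% answers; read two-sided, 9230 patients give 70%, not 80%, power for hospital mortality

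*Protocol*

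**What the plan says.** Protocol section 9.1 makes two calculations.

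- **ICU dependency (primary).** The aim is to detect, "with at least 80% power (two-tailed) and 95% certainty, a reduction in ICU dependency by one day". The result reads: "With a baseline mean ICU stay of 9 days in ICU and a standard deviation of 15, 2782 patients in each group are needed" for a one-day reduction, 5564 in total.
- **Hospital mortality (safety).** The aim reads: "To detect an adversely increased hospital mortality from 8.5% to 10% with 80% power and 95% certainty". The result is that "4612 patients per group need to be included (total 9224"). This is the larger requirement and is rounded up to the planned 9230.

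Two other sections bear on the sidedness of the tests. Section 3.1 states: "The study is two-tailed so that it is also powered to detect a negative impact of targeting normal blood glucose concentrations". Section 9.3 covers all outcomes, unadjusted and adjusted, and sets the threshold: "P-values will be considered significant when at or below 0.05 without correction for multiple testing". The protocol nowhere mentions a one-sided test or a 10% two-sided level.

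Section 9.1 also has the data monitoring committee compute a new sample size at 25% inclusion (n=2308) from control-group data. It gives no formula, significance level or sidedness for that step.

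**The concern.** A two-sided 5% test uses the critical value 1.960, a one-sided 5% test 1.645. With 80% power the choice changes the required size by about a fifth. The stated 2782 and 4612 are too small for a two-sided test on the stated inputs, although the first is labelled two-tailed in the same sentence.

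The mortality figure matters most, because it determines N. It serves a safety endpoint in a trial whose background section cites an earlier large trial that found higher mortality with tight control. If the test is two-sided, the risk of missing the stated increase is about 30% rather than the promised 20%.

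**Working it through.** **Inputs.** Section 9.1: difference 1 day, SD 15 days; mortality 8.5% and 10%; power 80% (z = 0.8416); 95% certainty, taken as alpha 0.05. Section 5.4: 1:1 allocation, so 9230 means 4615 per group. Critical values: 1.6449 one-sided, 1.9600 two-sided.

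**1. ICU dependency.** n per group = 2 × (z_alpha + z_beta)² × SD² / difference².

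- One-sided: 2 × (1.6449 + 0.8416)² × 225 = 2 × 6.1826 × 225 = **2782.2**. This is the protocol's 2782.
- Two-sided: 2 × (1.9600 + 0.8416)² × 225 = 2 × 7.8489 × 225 = **3532.0**, or 7064 in total.
- Shortfall: 1 − 2782/3532 = 21%.

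**2. Hospital mortality.** Pooled two-proportion formula with mean rate 0.0925:
n = [z_alpha × √(2 × 0.0925 × 0.9075) + z_beta × √(0.085 × 0.915 + 0.10 × 0.90)]² / 0.015².

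- One-sided: (0.67396 + 0.34473)² / 0.000225 = **4612.2**. This is the protocol's 4612.
- Two-sided: (0.80308 + 0.34473)² / 0.000225 = 5855.4, so **5856** per group, 11,712 in total.
- Shortfall: 1 − 4612/5856 = 21%.

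No usual variant rescues a two-sided reading: unpooled variance gives 5853, the arcsine method 5847, and a continuity correction 5988 per group.

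**3. Power at the planned size (4615 per group).**

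| Comparison | Two-sided 5% | One-sided 5% |
|---|---|---|
| One day, SD 15 | 89.3% | 94.0% |
| Mortality 8.5% v 10% | 70.1% | 80.0% |

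- One day, two-sided: standard error = 15 × √(2/4615) = 0.3123; 1/0.3123 − 1.960 = 1.242; power 89.3%. At the stated 2782 per group: standard error 0.4022; 1/0.4022 − 1.960 = 0.526; power 70.1%.
- Mortality, two-sided: (0.015 × √4615 − 0.80308) / √(0.085 × 0.915 + 0.10 × 0.90) = (1.01901 − 0.80308) / 0.40960 = 0.527; power 70.1% (68.8% with continuity correction).
- Raising the second rate until two-sided power reaches 80% gives about 10.2% (power 80.1% at 8.5% v 10.2%).

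**4. Margin for the primary endpoint.** At 4615 per group, two-sided power for one day falls below 80% only if the SD exceeds 15 × √(4615/3532) = 17.1 days.

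**The case against.** The strongest counter-argument concerns mortality. Section 9.1 attaches the two-tailed label only to ICU dependency. Its mortality sentence is directional, and sections 8.1 and 8.3 plan to stop on mortality only if the intervention is clearly inferior. In section 3.1 the two-tailed statement follows the null hypothesis on the primary outcome measures, and mortality comes afterwards as a safety endpoint. If a one-sided 5% test for harm was meant, 4612 is correct and 9230 patients do give 80.0% power.

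This stands as a plausible reading, so the 70% is conditional. It does not settle the matter. Section 3.1 speaks of the study as a whole and gives detection of harm as the reason for two tails. Section 9.3 lists chi-square tests, whose ordinary P-value is two-sided, and applies the 0.05 threshold to all outcomes. Nothing declares an exception for mortality. Nor does the argument reach the 2782, which is labelled two-tailed outright.

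A second objection is that 2782 does not set N, so its error costs no power at 9230. That is true. It remains a wrong figure in the central sample-size statement.

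A reader might infer two further things that the protocol does not support:

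- *That the 25% re-estimation will repeat the error.* No formula is stated for it, so reuse is conjecture. For the one-day effect at SD 15, moreover, both 5564 and 7064 lie below 9230.
- *That the weakness substudy in section 6.4 is a third instance.* It says "minimum 424 patients need to be included" for a 12% difference but gives no base rate. A two-sided calculation gives that total at 32.7% v 20.7% and equally at 79.3% v 67.3%; a one-sided one gives it at 52% v 40%. These rates are assumptions, and the figure is evidence neither way.

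**Conclusion.** The point holds. The ICU-dependency size is wrong as labelled: 2782 per group is the one-sided 5% answer, and the declared two-tailed calculation needs 3532. The mortality size of 4612 is likewise one-sided. Under the two-tailed design of section 3.1 and the threshold of section 9.3, the 80% power claimed for 8.5% against 10% is 70%.

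The consequence is limited. The primary endpoint is not underpowered: on the protocol's assumptions of a one-day effect and an SD of 15, it has 89% two-sided power at 9230. The mortality shortfall is ten percentage points of power, equivalent to detecting 10.2% rather than 10.0%, and disappears if a one-sided test for harm is declared consistently. All figures use the protocol's own effect sizes and variability with standard normal-approximation formulas.

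**What to change.** Keep N at 9230 and amend the text.

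1. **Section 9.1, ICU dependency.** Replace 2782 per group (5564) with 3532 per group (7064). State that 9230 gives 89% two-sided power for one day at SD 15.
2. **Section 9.1, mortality.** Choose one:
   - keep the two-sided test and state power of 70% for 8.5% v 10%, or 80% for 8.5% v about 10.2%; or
   - declare the calculation one-sided at 5% for harm, and make matching edits in sections 3.1 and 9.3. Changing 9.1 alone would leave it in conflict with both.
3. **Section 9.1, re-estimation.** State that it uses the two-sided 5% formula. This is a safeguard only.

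The cost is wording, with no extra patients. On the first mortality option the stated power becomes less favourable. Restoring 80% two-sided power for 8.5% v 10% would instead take 11,712 patients, 2482 more than planned; the correction does not require this.

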## 9.2 Randomization

The randomization procedure is described under heading 5.4. Patients will be stratified according to primary diagnostic category on ICU admission. Patients and family members will be blinded to treatment assignment. Due to the nature of the study, blinding physicians and nurses is not possible. Outcome assessors will be blinded, however.

## 9.3 Analysis

A Consolidated Standards of Reporting Trials (CONSORT) diagram will be reported.

For the primary and most secondary endpoints taking place during ICU stay, all data will be available. Of the secondary endpoints, some laboratory measurements may be missing. Missing data for one time point may be interpolated, by calculating the mean of the two neighbor measurements. In other cases, missing data will not be imputed.

All analyses will be done on intention to treat basis. In case of request for discontinuation of the study intervention by the patient or legal representative, this will be respected, but all data that are already collected will be analyzed.

The data file will be finalized and locked 90 days after inclusion of the last patient (except for the post ICU follow-up outcome parameters, as specified above). Discrete variables will be summarized by frequencies and percentages. Continuous variables will be summarized by use of either mean and standard deviation (SD) or median and interquartile range as appropriate. Results will be analyzed with the use of Chi-square testing, Student's t test or non-parametric testing (Wilcoxon rank-sum test, Van der Waerden test or Median test), as appropriate. Time-to-event effects will be documented by Kaplan-Meier plots with use of log-rank/Wilcoxon testing; the time-to-event effect size will be estimated with the use of Cox proportional hazard analysis provided the proportional hazard assumption is valid for the dataset. All time-to-event analyses will also be performed on data censored at 90 days. As death is a competing risk for duration of care outcomes, non-survivors will be censored beyond the longest duration of such care required for survivors.

All outcomes will be analyzed in an uncorrected manner as well as adjusted for baseline risk factors (including type and severity of illness, age, gender, body mass index, history of diabetes or not, center). For these analyses, P-values will be considered significant when at or below 0.05 without correction for multiple testing. To assess whether any eventual impact of the intervention on the primary and safety endpoints is affected by the baseline risk factor subgroup, interaction P-values will be calculated (logistic regression or Cox proportional hazard analysis as appropriate) with a threshold for significance of interaction set at a P-value of <0.1. These a

priori defined subgroups are: patients after cardiac surgery as compared with all other patients; patients admitted after elective surgery as compared with all other patients; patients admitted after surgery as compared with all other patients; patients with and without sepsis upon admission; patients with or without a known history of diabetes and/or an elevated HbA1c upon admission; patients admitted for a neurological/neurosurgical reason as compared with all other patients; patients admitted with brain injury as compared with all other patients; patients with high severity of illness score upon admission (APACHE-II  $\geq 20$ ) versus all other patients. Likewise, to study whether the intervention has a different effect in short-stay versus long-stay patients (ICU stay  $>3$  days), an interaction P-value will be calculated.

Prior to study termination and analysis of the results on short-term outcome, a full statistical analysis plan will be published.

## **10. Quality assurance**

To aid in achieving tight blood glucose control within the healthy fasting ranges and to reduce the risk of hypoglycemia and of blood glucose variability, blood glucose control will be guided by the LOGIC-insulin software. We previously demonstrated efficacy and safety of the LOGIC-insulin algorithm in a multicenter trial (20). As mentioned above, the software also advises on when to perform a next blood glucose measurement. The LOGIC-insulin software serves an advisory role. Eventually, the bedside nurse and physician have the possibility to overrule the given advice. However, our previous studies revealed a very high compliance rate.

As the difference in feeding regimen may be an important factor explaining the divergent outcomes of previous RCTs, the feeding intake needs to be standardized. In recent years, several studies have shown clinical advantage of a nutritional regimen that withholds parenteral nutrition in the acute phase of critical illness (first week in ICU).

## **11. Direct access to source data and documents**

The sponsor will provide direct access to the case record form (CRF), the source data and the study master file for monitoring, independent Ethics Committee review and regulatory inspection.

## **12. Ethics and regulatory approvals**

The trial will be conducted in compliance with the principles of the Declaration of Helsinki (2013), the principles of GCP and in accordance with all applicable regulatory requirements. This protocol and related documents will be submitted for review to the (local) Ethics Committee and to the Federal Agency for Medicine and Health Products for Clinical Trial

Authorization. Any subsequent protocol amendment will be submitted to the (local) Ethics Committee and Regulatory Authorities for approval. Required progress reports and a copy of the final study report will be provided to the (local) Ethics Committee and the Federal Agency for Medicine and Health Products.

The Study can and will be conducted only on the basis of informed consent by the subjects or their legal representatives to participate in the Study. The Participating Site will perform maximal efforts to obtain a signed informed consent form (ICF) for all patients within 72 hours after their enrollment and participation in the Study in compliance with all applicable laws, regulations and the approval of the (local) Ethics Committee. If necessary, the legal representative will be contacted by phone to obtain informed consent, which will be followed by a request to resend a written informed consent. The Participating Site will retain such ICFs in accordance with the requirements of all applicable regulatory agencies and laws.

The Investigator and the Participating Site shall treat all information and data relating to the Study disclosed to Participating Site and/or Investigator in this Study as confidential and shall not disclose such information to any third parties or use such information for any purpose other than the performance of the Study. The collection, processing and disclosure of personal data, such as patient health and medical information is subject to compliance with applicable personal data protection and the processing of personal data (Directive 95/46/EC and Belgian law of December 8, 1992 on the Protection of the Privacy in relation to the Processing of Personal Data)

Electronic data collection will be used. Data will be collected in a CRF, unambiguously linked to the source file. For reasons of data integrity and internal control during data input, the patient name is stored in a separate table linked to the eCRF. However, these data will only be accessible for the authorized local research staff and the principal database manager on a login/password base. When the database is finalized, the identity data will be blinded from the eCRF and only accessible by the study monitor or his substitute.

The sponsor will provide direct access to the CRF, the source data and the study master file for monitoring, independent Ethics Committee review and regulatory inspection. The sponsor will establish a data monitoring committee. The sponsor appointed a monitor ([name]). The monitor will verify that the trial is performed in accordance to the protocol as described in the European Medicine Agency's 'Note for guidance on good clinical practice CPMP/ICH/135/95' as well as the Declaration of Helsinki.

